## Therapeutic procedure after 6 weeks of erlotinib therapy

Only patients with documented (clinical examination, CT, PET) tumor control under erlotinib therapy (CR, PR or, at least, SD in the restaging procedures in week 7) will continue erlotinib therapy until progression of disease. In all patients with documented progress after 6 weeks of therapy erlotinib therapy will be stopped. Further treatment in these patients depends on overall performance state and declared intention of the patient. If the patient and the principal investigator or one of the co-investigators agree upon chemotherapeutic treatment, this treatment will be offered to the patient in the Department I of Internal Medicine, University Clinic Cologne.

## 5.10 Follow-up examinations after end of treatment

### Follow-up examinations

A standardized patient visit on month 3, 6, 9 and 12 comprises the following examinations:

- CT scan of the involved area
- Clinical examination including physical examination:
  - height, weight, vital signs, ECOG performance status
- Assessment of the neurological status
- Existing signs and symptoms
- Concomitant medication
- Laboratory assessment including:
  - blood count including differential count
  - serum electrolytes (Na, K, Ca),
  - liver function parameters (total bilirubin, ASAT, ALAT, AP,  $\gamma$ GT, LDH),
  - renal function parameters (creatinine, BUN, uric acid),
  - ESR
  - CYFRA 21-1, CEA

## 6 ADVERSE EVENTS

### 6.1 Handling of Safety Parameters

#### Serious Adverse Events

Any clinical adverse event or abnormal laboratory test value that is serious occurring during the course of the study, irrespective of the treatment received by the patient, must be reported to the trial coordinating center within one working day of knowledge (expedited reporting).

## ADVERSE EVENTS

The definition and reporting requirements according to German Drug Law, GCP-V and ICH Guideline for Clinical Safety Data Management, Definitions and Standards for Expedited Reporting, Topic E2 will be adhered.

Any serious adverse event that is unequivocally due to disease progression should not be reported as an AE. It will be documented in the regular CRF. Laboratory abnormalities of at least grade 2 NCI-CTCAE v3.0 will be documented as AEs.

The trial coordinating center will forward any clinical adverse event or abnormal laboratory test value that is serious to Roche within one working day.

The contact person is:

[name], [name]

Abt. Hämatologie/Onkologie

[name]

[name]

Fax-Nr: [name]

Roche will fulfill reporting requirements to authorities and ethics committees. SUSARs will be distributed to ethics committees and centers by Roche.

## **Treatment and Follow-up of Adverse Events**

Adverse events, especially those for which the relationship to test "drug" is not "unrelated", should be followed up until they have returned to baseline status or stabilized. If a clear explanation is established it should be recorded on the CRF.

## **Follow-up of Abnormal Laboratory Test Values**

In the event of unexplained abnormal laboratory test values, the tests should be repeated immediately and followed up until they have returned to the normal range and/or an adequate explanation of the abnormality is found. If a clear explanation is established it should be recorded on the CRF.

## **Pregnancy**

A female subject must be instructed to stop taking the test "drug" and immediately inform the investigator if she becomes pregnant during the study. Pregnancies occurring up to 90 days after the completion of the test "drug" must also be reported to the investigator. The investigator must report all pregnancies within one working day to the sponsor. The investigator should counsel the subject, discuss the risks of continuing with the pregnancy

and the possible effects on the fetus. Monitoring of the patient should continue until conclusion of the pregnancy.

Pregnancy occurring in the partner of a subject participating in the study should also be reported to the investigator and the sponsor. The partner should be counseled and followed as described above.

## 6.2 Definitions

An adverse event is any untoward medical occurrence in a patient or clinical investigation subject, administered a pharmaceutical product and which does not necessarily have to have a causal relationship with this treatment.

Adverse reactions are all untoward and unintended responses to an investigational medicinal product related to any dose administered.

A serious adverse event or serious adverse reaction is any experience that suggests a significant hazard, contraindication, side effect or precaution. It is any adverse event that at any dose fulfills at least one of the following criteria:

- is fatal (results in death)  
*(NOTE: death is an outcome, not an event)*
- is life-threatening  
*(NOTE: the term "life-threatening" refers to an event in which the patient was at immediate risk of death at the time of the event; it does not refer to an event which could hypothetically have caused a death had it been more severe.)*
- required in-patient hospitalization or prolongation of existing hospitalization
- results in persistent or significant disability/incapacity
- is a congenital anomaly/birth defect
- is medically significant or requires intervention to prevent one or other of the outcomes listed above

Medical and scientific judgment should be exercised in deciding whether expedited reporting to the sponsor is appropriate in other situations, such as important medical events that may not be immediately life-threatening or result in death or hospitalization but may jeopardize the patient or may require intervention to prevent one of the outcomes listed in the definitions above. These situations should also usually be considered serious.

Examples of such events are intensive treatment in an emergency room or at home for allergic bronchospasm; blood dyscrasias or convulsions that do not result in hospitalization; or development of drug dependency or drug abuse.

An unexpected adverse event is one, the nature or severity of which is not consistent with the applicable product information.

Causality is initially assessed by the investigator. With respect to report and documentation obligation (regulatory authorities, ethics committees and other investigators) for Serious Adverse Events, causality can be one of 2 possibilities:

- No (unrelated; equals not drug related).

## ADVERSE EVENTS

- Yes (remotely, possibly, probably or definitely drug related).

All adverse events not assessed as definitive "not drug related" by either the investigator or Roche will be considered as adverse drug reaction.

A suspected unexpected serious adverse reaction (SUSAR) is a serious adverse reaction, the nature, or severity of which is not consistent with the applicable product information.

It is important that the severity of an adverse event is not confounded with the seriousness of the event. For example, vomiting which persists for many hours may be severe, but is not necessarily a serious adverse event. On the other hand, stroke which results in only a limited degree of disability may be considered a mild stroke, but would be a serious adverse event.

A serious adverse event occurring during the study or which comes to the attention of the investigator within 28 days after stopping the treatment, whether considered treatment-related or not, must be reported. In addition, a serious adverse event that occurs after this time, if considered related to test "drug", should be reported.

Such preliminary reports will be followed by detailed descriptions later which will include copies of hospital case reports, autopsy reports and other documents.

For serious adverse events, the following must be assessed and recorded on the adverse events page of the Case Report Form: intensity, relationship to test substance, action taken, and outcome to date.

Document and report obligation have to be adhered according to the national and international laws and regulations.

### **6.3 Treatment postponement, dose reduction and termination.**

In case of any adverse event, which may be classified by the investigators as an suspected drug reaction and is not controlled by optimal supportive care, or not tolerated due to symptoms, disfigurement, or interference with normal daily activities, Tarceva® dose may be reduced according to the following schedule:

Starting dose: 150 mg

First reduction: 100 mg

Second reduction: 50 mg.

Within further 2 weeks after dose reduction, the adverse event must have been improved at least by one NCI-CTC grade to NCI-CTC grade < 2. Otherwise, a further dose reduction must be performed. The dose interruption may last maximal 2 weeks if clinically indicated and if the toxicity is not controlled by optimal therapy.

Once a dose was reduced due to toxicity, the dose will not be reescalated, except for Tarceva® induced rash. In case of rash, the dose can be reescalated if the rash is < grade 2 NCI-CTC.

In case of skin reaction and diarrhoea the following dose management and therapy is indicated:

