## ADVERSE EVENTS

| NCI – CTC Grade                                                    | Dose Modification                                    | Recommended Therapy                                                                                      |
|--------------------------------------------------------------------|------------------------------------------------------|----------------------------------------------------------------------------------------------------------|
| RASH                                                        |                                                      |                                                                                                          |
| grade 1                                                            | None                                                 | None                                                                                                     |
| grade 2                                                            | None                                                 | minocycline p.o., tetracycline topical, clindamycin topical, silver sulfadiazine topical, prednison p.o. |
| grade 3                                                            | dose reduction, re-escalation by rash $\leq$ grade 2 | as above                                                                                                 |
| grade 4                                                            | off study                                            |                                                                                                          |
| DIARRHEA                                                    |                                                      |                                                                                                          |
| grade 1 (stools < 4)                                               | None                                                 | loperamide                                                                                               |
| grade 2 (4 – 6 stools)                                             | None                                                 | loperamide                                                                                               |

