### **Inclusion in the analysis**

Full analysis set (primary analysis, intention-to-treat): All patients included in the study will be analysed (contingent on availability of endpoints). Per-protocol set (secondary analysis): Only patients fully compliant with the protocol (especially regarding dosage) will be analysed. The full analysis set will be taken as safety analysis population as all patients will receive the study medication.

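### Section 6.3 contradicts itself on a rash that has improved to grade 2 after a dose reduction: the text withholds re-escalation, the table provides for it, and neither is given precedence

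*Protocol*

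**What the plan says.** The text of Protocol section 6.3 contains three rules that bear on a rash after a dose reduction.

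- A general ban on re-escalation with one exception: "Once a dose was reduced due to toxicity, the dose will not be reescalated, except for Tarceva® induced rash".
- The condition on that exception: "In case of rash, the dose can be reescalated if the rash is < grade 2 NCI-CTC".
- A two-week rule, written for adverse events in general. Within a further two weeks of a reduction, "the adverse event must have been improved at least by one NCI-CTC grade to NCI-CTC grade < 2". The next sentence reads: "Otherwise, a further dose reduction must be performed".

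The text then brings in the dose-modification table: "In case of skin reaction and diarrhoea the following dose management and therapy is indicated". In that table, the row for grade 3 rash says "dose reduction, re-escalation by rash $\leq$ grade 2".

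Section 7.4 (Inclusion in the analysis) makes the full analysis set primary. Of the secondary per-protocol set it says "Only patients fully compliant with the protocol (especially regarding dosage) will be analysed".

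**The concern.** Text and table govern the same patients, and they differ on whether grade 2 is good enough for the dose to go back up. Two physicians following section 6.3 faithfully could therefore handle the same patient differently. This is a stated dosing rule that contradicts itself, not a detail left for later.

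The first thing at stake is a safety instruction, part of it mandatory. The second is how the trial is read afterwards. If per-protocol membership turns on dosage, the same dosing can count as compliant under one part of section 6.3 and as a deviation under the other.

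**Working it through.** No sample size, power or significance level is involved. The check applies both rules to the same patient and then sizes the group affected.

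**Step 1. Apply both rules by grade.** The patient had grade 3 rash and the dose was reduced.

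| Rash now | Text of 6.3 | Table of 6.3 | Result |
|---|---|---|---|
| Grade 1 | Below 2: re-escalation permitted | At or below 2: re-escalation provided for | Agree |
| Grade 2, before the two-week check | Not below 2: re-escalation withheld | At or below 2: re-escalation provided for | Thresholds conflict |
| Grade 2, at the two-week check | Re-escalation withheld; further reduction required | Re-escalation provided for | Opposite directions |
| Grade 3 | Re-escalation withheld; further reduction required at the check | No re-escalation; the row says reduce | Agree |

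The third row needs both parts of the two-week requirement. Going from grade 3 to grade 2 is an improvement of 3 − 2 = 1 grade, so the first part is met. Grade 2 is not below 2, so the second part fails and the further reduction follows.

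**Step 2. Translate into the listed dose steps.** Section 6.3 lists 150 mg, 100 mg and 50 mg. For a patient at 100 mg after a first reduction and still at grade 2 at the check, the text leads to 50 mg. The table leads upward from 100 mg; it does not name the target, and 150 mg is the only higher step listed.

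**Step 3. Look for a tie-breaker.** No passage ranks text against table, and none exempts rash from the two-week rule. Preferring the specific rule to the general does not settle the threshold, because the text's re-escalation sentence is itself specific to rash.

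**Step 4. Rule out a reading error in the file.** The text gives the strict sign twice, once in the rash sentence and once in the two-week rule. The table keeps its own sign in both the rash and the diarrhoea rows. In whole grades, the diarrhoea row's limit of at most 1 is the same as below 2, so that row matches the grade limit in the text and only the rash row departs from it.

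**Step 5. Size.**

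- Grade 3 rash rate: 8%, from the adverse-reaction table in section 5.9 (Side effects), which cites the phase III trial in previously treated patients.
- Planned patients: 40 (synopsis; section 3.2).
- Expected patients with grade 3 rash: 0.08 × 40 = 3.2.

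This is a ceiling on the expected number affected. Only those who are reduced and then improve to exactly grade 2 meet the conflict, and only those still at grade 2 two weeks after the reduction meet the opposite instructions. The documents give neither fraction, so the range is 0 to about 3.

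**Step 6. Timing.** Section 5.9 gives a median onset of rash of 8 days. If, for illustration, the dose is reduced at that point, the check falls at 8 + 14 = day 22 of the 42-day course. That is after the early PET window (days 7 to 14) and before the week 7 CT.

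**The case against.** The strongest reply is that the quoted rash sentence shows only a mismatch of thresholds. Opposite instructions need the two-week rule as well, and that rule stands in the general paragraph on adverse events. Since the text presents the table as the management indicated for skin reactions, a reader could take the table to replace the general two-week step for rash. The dispute would then be only whether the dose may rise at grade 2, not whether it goes up or down.

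This stands in part. The opposition is conditional on the two-week rule applying to rash and on the rash still being grade 2 at the check. It does not remove the threshold conflict, because the sentence that excludes grade 2 is about rash. Nor does the text's permissive wording help: it permits re-escalation only below grade 2.

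A second reply is that the trial has one center and that any grade 3 toxicity goes to the principal investigator within 24 hours (section 6.3). That makes uneven handling less likely, and a reader should not infer a spread of practice across sites. It supplies no rule, however.

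A third reply concerns the per-protocol set. It is secondary, and section 7.4 does not say whether any permitted dose modification counts as full compliance, so part of that question exists whichever rash threshold applies. Detailed per-protocol rules may also stand in an SAP that is not shown. This stands: a reader might infer that the per-protocol set is undefined, but the documents support only that membership is ambiguous for the few patients affected.

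**Conclusion.** The contradiction is real and narrow. At grade 2 after a reduction from grade 3, the text of section 6.3 withholds re-escalation and its table provides for it. At the two-week check, if the general rule applies to rash, the text also requires a further reduction. At grades 1 and 3 the two agree on direction.

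The size is about 0 to 3 of 40 patients. This assumes that the 8% rate from relapsed disease applies to untreated patients over six weeks. It would be wrong to read 3.2 as a forecast of patients receiving conflicting instructions, since it counts everyone expected to have grade 3 rash.

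A reader might also infer damage to the primary result. The documents do not support that. The full analysis set is primary, and on the illustrative timing the early PET precedes the check. Dose in the later weeks, before the week 7 CT, could differ with the rule followed, but no effect on the AUC has been shown. The case for acting rests on the safety instruction: even one patient can meet two incompatible rules in one section.

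**What to change.** The investigators should reconcile the text and table of section 6.3 to a single rash rule: one re-escalation threshold, worded identically in both places, with a statement of whether the two-week rule applies to rash. Which threshold is right is a clinical decision on which this review takes no view.

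Per-protocol dosage compliance under section 7.4 should then be judged against that single rule, by a cross-reference there or in the SAP.

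The cost is a wording amendment, with ethics and regulatory approval if section 10.1 requires it, and notice to staff at the one center. Sample size, visits and the primary analysis are unchanged.

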## ADVERSE EVENTS

| NCI – CTC Grade                                                    | Dose Modification                                    | Recommended Therapy                                                                                      |
|--------------------------------------------------------------------|------------------------------------------------------|----------------------------------------------------------------------------------------------------------|
| RASH                                                        |                                                      |                                                                                                          |
| grade 1                                                            | None                                                 | None                                                                                                     |
| grade 2                                                            | None                                                 | minocycline p.o., tetracycline topical, clindamycin topical, silver sulfadiazine topical, prednison p.o. |
| grade 3                                                            | dose reduction, re-escalation by rash $\leq$ grade 2 | as above                                                                                                 |
| grade 4                                                            | off study                                            |                                                                                                          |
| DIARRHEA                                                    |                                                      |                                                                                                          |
| grade 1 (stools < 4)                                               | None                                                 | loperamide                                                                                               |
| grade 2 (4 – 6 stools)                                             | None                                                 | loperamide                                                                                               |
| grade 3 (stools $\geq$ 7)                                          | Interrupt                                            | interruption until resolution to grade $\leq$ 1, restart at reduced dose                                 |
| grade 4
(life threatening sequelae, e.g. haemodynamic collapse) | off study                                            |                                                                                                          |

Patients requiring a dose interruption for > 2 weeks due to not controlled adverse events of the Tarceva® medication will be taken off study.

In any case of a grade IV toxicity the patient will be withdrawn from the study. Any grade III toxicity will be reported to the principal investigator within 24 h after notice.

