### **3.4 Termination of protocol treatment**

The patient can discontinue trial participation at his/her own wish at any time. Protocol treatment can be terminated based upon the decision of the treating physician, due to unacceptable toxicity, progression, serious intercurrent disease or pregnancy. In any case, following a formal or an actual termination, the patient's follow up should be documented.

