**5.7 Patient briefing and termination of protocol treatment**

After completion of staging, the patient is informed about the trial, including the following aspects: title and aim of the trial, nature of the treatment, side effects, reason for recruitment, passing on of data and material samples, insurance, the ethics committee vote and the patient's freedom to decide. The patient receives an information brochure and an informed consent form.

The signed original consent form and the record of the briefing remain in the patient's files. The patient will receive a copy of each document.

The patient can make a free decision on participation in the trial at any time. If trial participation is refused, the treatment can be freely chosen in accordance with the treating physician.

Termination of protocol treatment can occur at the patient's wish or if the treating physician decides to terminate it due to unacceptable toxicity, serious concurrent disease or pregnancy. Documentation after termination will be performed

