## Analysis of secondary endpoints

The prognostic value/accuracy of FDG/FLT-PET regarding clinical failure, SD and clinical response in NSCLC patients treated with erlotinib will be compared by ROC analysis; optimal cut-off values for FDG/FLT PET will be chosen (*secondary objective*).

Association between EGFR mutation, KRAS mutation and EGFR positivity with clinical response will be tested by Fisher's exact test.

Secondary endpoints (FFTF and OS) will be analyzed using descriptive statistics after at least one year follow-up of all patients.

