### **Reporting of results**

- All patients included in the study must be assessed for response to treatment, even if there are major protocol treatment deviations or if they are ineligible. Each patient will be assigned one of the following categories: 1) complete response, 2) partial response, 3) stable disease, 4) progressive disease, 5) early death from malignant disease, 6) early death from toxicity, 7) early death because of other cause, or 9) unknown (not assessable, insufficient data).
- All of the patients who met the eligibility criteria should be included in the main analysis of the response rate. Patients in response categories 4-9 should be considered as failing to respond to treatment (disease progression). Thus, an incorrect treatment schedule or drug administration does not result in exclusion from the analysis of the response rate. Precise definitions for categories 4-9 will be protocol specific.
- All conclusions should be based on all eligible patients.
- Subanalyses may then be performed on the basis of a subset of patients, excluding those for whom major protocol deviations have been identified (e.g., early death due to other reasons, early discontinuation of treatment, major protocol violations, etc.). However, these subanalyses may not serve as the basis for drawing conclusions concerning treatment

efficacy, and the reasons for excluding patients from the analysis should be clearly reported.

- The 95% confidence intervals should be provided.

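### Section 6.3 takes patients off the study where 3.4 and 5.7 end only protocol treatment, leaving open whether the week-7 CT is still done

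*Protocol*

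**What the plan says.** Section 6.3 (treatment postponement, dose reduction and termination) sets two general rules. One is "In any case of a grade IV toxicity the patient will be withdrawn from the study". The other begins "Patients requiring a dose interruption for > 2 weeks due to not controlled adverse events" and takes those patients off study. Its table uses the same off-study wording for grade 4 rash and grade 4 diarrhoea.

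Section 3.4 describes the consequence of toxicity differently: "Protocol treatment can be terminated based upon the decision of the treating physician, due to unacceptable toxicity". It then adds: "In any case, following a formal or an actual termination, the patient's follow up should be documented". Section 5.7 also lists toxicity as a ground for ending protocol treatment and closes with "Documentation after termination will be performed".

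Other parts of the protocol rely on the data being complete:

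- Section 7.4, on inclusion in the analysis, defines the primary set: "All patients included in the study will be analysed (contingent on availability of endpoints".
- Section 7.2 says FFTF and OS "will be analyzed using descriptive statistics after at least one year follow-up of all patients".
- The RECIST appendix in 12.3, under reporting of results, says: "All patients included in the study must be assessed for response to treatment, even if there are major protocol treatment deviations".

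**The concern.** Sections 3.4 and 5.7 separate stopping erlotinib from leaving the trial. Section 6.3 merges the two for toxicity. Someone applying 6.3 as written could reasonably conclude that no further study assessments are due.

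The week-7 CT is the item most exposed. It separates progressers from non-progressers, so a patient without it cannot enter the primary ROC analysis. It is a restaging procedure in 5.9, whereas the follow-up that 3.4 asks to have documented most naturally means the month 3 to 12 visits of 5.10. FFTF and OS are better protected by 3.4, but they are also exposed if off study is read as the end of observation.

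An analysis plan written later cannot repair this. It can say how to handle a missing CT, but it cannot recover one that was never taken. The protocol also points two ways on such a patient. Section 7.4 drops anyone without an endpoint, while the appendix counts unassessable patients as failures in the response rate. That second rule could label as progression a patient who stopped for toxicity with the tumour under control.

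**Working it through.** **1. The passages side by side**

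| Question | 6.3 | 3.4 and 5.7 |
|---|---|---|
| What does toxicity end? | Participation in the study | Protocol treatment |
| Are data collected afterwards? | Not stated | Follow-up or documentation continues |
| Is the week-7 CT still done? | Not stated | Not stated |

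**2. Reproducing the planned sample size (section 7.3)**

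Inputs from the protocol: AUC θ = 0.75 against 0.5; 16 non-progressers and 24 progressers, so k = 24/16 = 1.5; power 80%; one-sided 2.5% (7.2), which has the same critical value, 1.96, as a two-sided 5% test. The variance is the binormal approximation:

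V(θ) = 0.0099 · exp(−A²/2) · [(5A² + 8) + (A² + 8)/k], with A = 1.414 · z(θ).

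- At θ = 0.5: A = 0, V = 0.0099 × (8 + 8/1.5) = 0.132, √V = 0.363.
- At θ = 0.75: A = 1.414 × 0.6745 = 0.954, A² = 0.910, V = 0.0099 × 0.635 × (12.55 + 5.94) = 0.116, √V = 0.341.
- Non-progressers needed: [1.96 × 0.363 + 0.842 × 0.341]² / 0.25² = 15.97; total 15.97 × 2.5 = 39.9. The plan states 16 and 40.
- The other rows give totals of 63.5 (stated 64) and 26.9 (stated 27).
- Confidence-interval half-width: 1.96 × 0.341/√16 = 0.167 (stated 0.17).

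The plan's figures reproduce. They contain no allowance for missing outcomes, and section 3.2 caps recruitment at the same 40.

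**3. How many patients could be affected**

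The protocol gives no dropout rate. The only guide is the adverse-reaction table in 5.9.

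- Drug-typical events: grade 4 rash and diarrhoea are each below 1%, so below 0.4 patients each and under 1 of 40 together.
- Grade 4 dyspnoea counted as well: 11% × 40 = 4.4 patients.
- Dyspnoea 11%, fatigue 4% and anorexia 1%, with no overlap: 16% × 40 = 6.4 patients.

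Interruptions longer than two weeks would add a number the protocol does not allow one to estimate.

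**4. Power if week-7 CTs are missing**

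With m non-progressers and n progressers, and k = n/m:

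power = Φ{[√m × 0.25 − 1.96 √V(0.5)] / √V(0.75)}.

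With no loss, m = 16: (1.000 − 0.712)/0.341 = 0.845, giving 80.1%. With four lost in proportion, m = 14.4: (0.949 − 0.712)/0.341 = 0.694, giving 75.6%.

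| CTs lost | Proportional loss | All progressers | All non-progressers |
|---|---|---|---|
| 0 | 80.1% | 80.1% | 80.1% |
| 2 | 78.0% | 78.7% | 76.5% |
| 4 | 75.6% | 77.0% | 72.0% |
| 6 | 73.1% | 75.0% | 66.3% |

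These are powers for a single AUC, as the plan itself calculates.

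**5. Does the loss bias the AUC?**

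The AUC compares values between outcome classes, so thinning one class at random leaves it unchanged. In a simulation with a true AUC of 0.75 and 200,000 values per class, removing 20% of progressers at random gave 0.751. Removing the progressers with the most clearly progressive PET values gave 0.721 when 11% were lost and 0.692 when 20% were lost. Bias therefore needs loss that depends on the PET value within an outcome class. Response, SD, FFTF and OS rates have no such protection: loss related to outcome shifts them directly.

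**The case against.** The strongest reply is that 6.3 is about treatment. Its heading says so, and in its table the off-study entries sit in the dose-modification column, so off study drug is a natural reading. The trial has one centre, which limits divergent practice. Sections 3.4 and 5.7 call for documentation after termination. This much stands: the protocol does not establish that any outcome will be lost. It does not remove the conflict. The wording of 3.4 is a recommendation, that of 6.3 is an instruction, and neither mentions the week-7 CT.

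The size is also open to challenge. Section 6.3 speaks of suspected drug reactions, and much grade 4 dyspnoea or fatigue may come from the tumour. The table in 5.9 comes from patients who had already failed chemotherapy, while this trial enrols untreated patients for six weeks. The upper figure of 4 to 6 is therefore a scenario, not a forecast.

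A reader might infer four stronger things that the documents do not support:

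- That losing progressers biases the primary AUC. It does not by itself, as step 5 shows.
- That the loss is known to be tied to outcome. This is plausible for dyspnoea and fatigue, but the protocol does not say it.
- That safety follow-up is cut short. Section 6.1 asks for adverse events to be followed until they resolve or stabilise, and 6.2 requires serious events to be reported up to 28 days after stopping, and later if related.
- That one-year survival will be overstated by some definite amount. That would need an assumed survival in the removed patients and missing death dates, and 3.4 argues against the latter.

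**Conclusion.** The contradiction between 6.3 and sections 3.4 and 5.7 is real and should be resolved. Its main consequence is uncertainty over the week-7 CT, the reference standard for the primary endpoint, in patients removed for toxicity. FFTF and OS are a lesser exposure.

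The effect on the primary analysis is a modest loss of power: from about 80% to about 76% with four CTs missing and about 73% with six, assuming proportional loss at AUC 0.75. If only drug-typical grade 4 events trigger removal, fewer than 1 of 40 patients is affected and the loss is negligible. All of this rests on 6.3 being applied literally. Bias in the AUC is conditional on loss that follows the PET value within an outcome class. Distortion of the response, SD, FFTF and OS rates needs only loss related to outcome.

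**What to change.** Reconcile 6.3, including its table, with 3.4 and 5.7. State that the events listed there end erlotinib protocol treatment but not observation. Add that the week-7 CT already scheduled in 5.9 and the follow-up visits of 5.10 continue for these patients unless consent is withdrawn.

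Which toxicities lead to stopping, and all dose rules, remain the sponsor's decision and are not part of this point.

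The cost is a wording amendment. It adds no assessment, because the CT and the visits are already in every patient's schedule. With observation kept, the sample size of 40 and the planned power of about 80% stand unchanged as far as this point is concerned.
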